#### Interventions

Participants in the intervention group will receive iNO at 200 ppm two times daily, with each session lasting 30 min, for 5 days, beginning within 24 h of enrollment [8]. Both the intervention and control groups will receive standard treatment according to relevant guidelines for severe pneumonia. Standard treatment may include empirical and targeted anti-infective therapy, fluid resuscitation, vasoactive drugs, lung-protective ventilation, organ support, nutritional support, and immunomodulatory therapy as clinically indicated. Once antimicrobial susceptibility results are available, participants in both groups with confirmed MDR bacterial infection will continue the protocol-directed study intervention. For participants in whom MDR bacterial infection is not confirmed, the study intervention administered solely for research purposes will be discontinued in both groups.

Inhaled NO will be administered using the NOwill N300 Nitric Oxide Generation and Delivery System (Noling Biotechnology Co., Ltd., Nanjing, China). All device installation, mode selection, circuit connection, pre-treatment safety checks, and monitoring during treatment will be performed exclusively by designated independent research personnel who have completed manufacturer training and are qualified to operate the system. These personnel will not participate in participant screening, routine clinical care, outcome assessment, data collection, or statistical analysis.

At enrolment, inhaled NO will be delivered through the mechanical ventilator circuit. If a participant is extubated during the treatment period, inhaled NO will be administered through an interface compatible with the selected sequential oxygen therapy modality.

The NOwill N300 system may be connected to invasive ventilators, noninvasive ventilators, high-flow oxygen therapy systems, nasal cannulae, or face masks. For participants receiving invasive mechanical ventilation, the NO delivery device will be integrated into the ventilator circuit at the gas outlet, with a flow sensor and NO injection port installed. The NO injection port will be positioned upstream of the humidification chamber to enable NO delivery during the inspiratory phase.

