##### Secondary outcomes

 In-hospital mortality, ICU mortality, and 28-day mortality.Ventilator-free days, vasopressor-free days, antibiotic-free days, ICU-free days, and hospital-free days through day 28.CPIS and Sequential Organ Failure Assessment (SOFA) scores on days 3 and 7.Microbiological eradication rate on day 7.Concentrations of citrullinated histone H3 and cell-free DNA.Daily ratio of arterial oxygen partial pressure to fractional inspired oxygen (PaO_2_/FiO_2_) from days 1 to 7.

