##### Safety outcomes

Incidence of MetHb levels ≥5%, ≥7%, and ≥10%.Incidence of inhaled nitrogen dioxide (NO_2_) concentrations ≥3 ppm.Serum creatinine levels from days 1 to 7.Airway hyperreactivity events.Incidence of acute kidney injury (AKI), including stages 1, 2, and 3, during hospitalization.

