##### Safety monitoring

During inhaled NO administration, NO2 will be continuously monitored and maintained below 3 ppm. MetHb levels will be measured 15 min after the initiation of each inhaled NO treatment session and at the end of each session. Renal function will be assessed daily using blood testing. An independent Data and Safety Monitoring Board (DSMB), comprising two external clinicians and one biostatistician, will review safety data every 6 months. No formal interim analysis of efficacy or futility and no sample-size re-estimation are planned. Serious adverse events will be reported within 24 h. The final database will be locked upon completion of the 30-day follow-up and resolution of all queries. Participant recruitment and study-gas treatment will be temporarily suspended, and an ad hoc safety review by the Data and Safety Monitoring Board (DSMB) will be initiated, if any of the following occurs:Any unexpected death assessed as at least possibly related to study-gas treatment.Two or more unexpected serious adverse events assessed as at least possibly related to study-gas treatment.In the NO group, permanent discontinuation of study-gas treatment due to methemoglobin (MetHb) ≥7% or persistent inhaled NO_2_ concentrations >3 ppm in ≥10% of participants.A clinically important and unexpected imbalance between groups in the incidence of serious adverse events, severe hypoxemia, or hemodynamic instability.A major breach of blinding, major protocol deviation, or data-integrity issue that may jeopardize participant safety or seriously compromise trial validity.

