##### Statistical analysis

Statistical analyses will be performed using R in RStudio. Changes in CPIS, 28-day ventilator-free days, vasopressor-free days, antibiotic-free days, ICU-free days, hospital-free days, CPIS and SOFA scores, PaO_2_/FiO_2_ ratios, and serum creatinine levels will be assessed for normality. Normally distributed continuous data will be expressed as mean ± SD and compared between groups using the independent-samples t test. Non-normally distributed continuous data will be expressed as median and interquartile range, M (Q1, Q3), and compared using the Wilcoxon rank-sum test. In-hospital mortality, ICU mortality, 28-day mortality, the incidences of MetHb levels ≥5%, ≥7%, and ≥10%, inhaled NO_2_ concentrations ≥3 ppm, airway hyperreactivity events, and AKI stages 1, 2, and 3 during hospitalization will be expressed as *n* (%) and compared between groups using the chi-square test or Fisher’s exact test, as appropriate. A P value less than 0.05 will be considered statistically significant.

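### AKI is counted over each participant's whole hospital stay and compared as a crude proportion, so discharge and death set the time at risk; scheduled creatinine covers only days 1 to 7

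*Protocol article*

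**What the plan says.** All references are to the protocol article.

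- **Outcome window.** Safety outcomes lists "Incidence of acute kidney injury (AKI), including stages 1, 2, and 3, during hospitalization". No last day is given. The same list has "Serum creatinine levels from days 1 to 7" as a separate outcome.
- **Schedule.** In Table 1 the creatinine row is marked on days 1 to 7 only. The AKI row is marked on days 1 to 7 and again at ICU discharge and hospital discharge.
- **Renal monitoring.** Safety monitoring states: "Renal function will be assessed daily using blood testing". It names no end day.
- **Analysis.** Statistical analysis states that "AKI stages 1, 2, and 3 during hospitalization will be expressed as *n* (%) and compared between groups", using the chi-square test or Fisher's exact test. Time at risk and death are not mentioned.
- **Outcomes that set the window.** Secondary outcomes includes "In-hospital mortality, ICU mortality, and 28-day mortality" and also "Ventilator-free days, vasopressor-free days, antibiotic-free days, ICU-free days, and hospital-free days through day 28". The free-day outcomes stop at day 28; AKI does not.
- **Exposure.** Interventions gives study gas twice daily, "with each session lasting 30 min, for 5 days, beginning within 24 h of enrollment".
- **Lock.** Safety monitoring states: "The final database will be locked upon completion of the 30-day follow-up and resolution of all queries". The last dated column of Table 1 is day 28.

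**The concern.** A crude proportion compares like with like only if both arms are watched for the same length of time. Here a participant who dies on day 3 or leaves on day 10 has much less opportunity to be counted than one who stays 40 days, and the length of that opportunity is itself an outcome of the trial. If NO shortened stay, counted AKI would fall with no renal benefit. If NO kept more patients alive in hospital, counted AKI would rise with no renal harm. The renal safety statement could be wrong in either direction.

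The measurement behind the staging is also uneven. Daily creatinine is scheduled for the first week, after which the schedule asks for AKI staging at two discharge points without a creatinine entry to support it. The gas course lasts at most 5 days, so the period best covered by scheduled data is also the period closest to exposure.

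**Working it through.** **Is there a figure to reproduce?** Not for AKI. The document gives no AKI rate, no expected length of stay and no power for AKI. Its only calculation is the sample size for the primary outcome, which does not bear on this point. The hazards and stays below are assumptions.

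**Model.**
- AKI hazard h per hospital day, constant and identical in both arms, so NO has no renal effect.
- Exit from hospital, by discharge or death, is exponential with mean stay L.
- AKI counted over the open stay: h / (h + 1/L).
- AKI counted in hospital by day 7: [h / (h + 1/L)] × [1 − exp(−7(h + 1/L))].

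**Numbers put in.** Mean stays of 20 and 28 days, so 1/L = 0.0500 and 0.0357. Example at h = 0.01:
- Open stay: 0.01/0.0600 = 16.7% and 0.01/0.0457 = 21.9%.
- By day 7: 0.167 × (1 − exp(−0.42)) = 5.7% and 0.219 × (1 − exp(−0.32)) = 6.0%.

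| h per day | Open stay, 20 vs 28 days | Difference | By day 7, 20 vs 28 days | Difference |
|---|---|---|---|---|
| 0.010 | 16.7% vs 21.9% | 5.2 points | 5.7% vs 6.0% | 0.3 points |
| 0.015 | 23.1% vs 29.6% | 6.5 points | 8.4% vs 8.8% | 0.4 points |
| 0.020 | 28.6% vs 35.9% | 7.3 points | 11.1% vs 11.6% | 0.5 points |

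**Other stays, same model.** With h from 0.01 to 0.03 and one arm at a mean of 20 days:
- If the other arm averages 30 days, the open-stay risk ratio is 1.26 to 1.38, against 1.05 to 1.06 by day 7.
- If it averages 15 days, the open-stay ratio is 0.78 to 0.83, against about 0.95 by day 7.
- With 49 per arm (half of the roughly 98 to be enrolled), 20 versus 30 days would reject equality 12% to 16% of the time instead of the nominal 5%.

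**Share of counted AKI after scheduled creatinine ends.** In this model the share after day 7 is exp(−7(h + 1/L)). At L = 20 it is exp(−0.42) = 66% for h = 0.01 and exp(−0.49) = 61% for h = 0.02.

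**Lock.** About 98 enrolled over 18 months is 98/18 = 5.4 per month. If 20% to 40% of the last month's recruits (assumed) were still in hospital at day 30, that is 5.4 × 0.2 = 1.1 to 5.4 × 0.4 = 2.2 participants.

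**The case against.** **Later testing is not ruled out.** A reader might infer that after day 7 an AKI stage depends on whether someone happens to order a test. The text does not support that: Safety monitoring promises daily renal blood testing with no end day, and Table 1 stages AKI at both discharges. What stands is that this sentence and the creatinine row of Table 1 do not agree. Even daily testing to discharge would leave the observation windows unequal.

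**A fixed-window renal comparison already exists.** Creatinine on days 1 to 7 is its own outcome and is compared between groups. Mortality and hospital-free days are reported, so a careful reader could see differences in survival and stay. The documents nowhere rank in-hospital AKI as the main renal harm result, and it should not be called that. This limits the damage, but AKI incidence is still the renal outcome that will be quoted as a percentage with a P value.

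**Counting to discharge captures later harm.** That is a fair aim, and it is met if the count is kept as a description.

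**Day 7 does not remove death.** Correct: a death on day 3 falls inside that window too. This is why deaths by day 7 belong beside the AKI result.

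**The size is assumed.** Also correct. Putting the mean stay straight into 1 − exp(−hL) would give 6 to 10 points, but that treats everyone in an arm as staying equally long; exponential stays give 5 to 7. A hazard that falls after the first week would shrink it further.

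**The lock cuts nobody at day 30.** A reader might take the 30-day sentence to truncate each participant's AKI and in-hospital mortality. It describes one trial-level event; earlier recruits with long stays can be fully observed.

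**Conclusion.** The point holds on the protocol's own text. The window, the measurement schedule and the test are all stated, and they do not fit together: an open-ended count, scheduled creatinine for one week, and a crude proportion that ignores time at risk. Length of stay and survival therefore enter the AKI comparison.

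The direction and size of any bias cannot be known from the documents. The 5 to 7 points rest on an equal constant hazard of 1% to 2% per day and exponential stays of mean 20 versus 28 days, none of which the protocol states. The contrast with under 1 point by day 7 is the useful result. If mean stays turn out equal across arms, this model gives no artefact.

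This is a change worth making, not a fatal flaw. It concerns one of five listed safety outcomes and leaves the primary outcome and the sample size untouched. The mismatch between 28 and 30 days is minor: on the assumption above it could affect in-hospital outcomes for 1 or 2 participants.

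**What to change.** 1. **Safety outcomes and Statistical analysis.** Make the between-group AKI comparison the highest stage reached from first study gas to day 7, the window covered by scheduled creatinine. Report deaths by day 7 in each arm beside it.
2. **AKI to hospital discharge.** Keep it as a descriptive count by stage, without a test.
3. **Table 1 and Safety monitoring.** Reconcile the creatinine row, which ends at day 7, with the undated daily renal testing, and state what data support the AKI stage recorded at ICU and hospital discharge.
4. **Database lock (minor).** Either state that lock follows day 28 and the discharge or death of the last participant, or cap in-hospital mortality, ICU mortality and AKI at day 28 for everyone. Remove or explain the 30-day follow-up.

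Cost: wording only for items 1 and 2, which use measurements already scheduled. The downside is small: AKI after day 7 is described and not tested. Under the first lock option, the lock may wait for the last inpatients.

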##### Analysis of populations

Three analysis populations will be defined: the modified intention-to-treat population with confirmed MDR pathogens (mITT-MDR), the per-protocol population with confirmed MDR pathogens (PP-MDR), and the safety population [24].

The safety population will include all randomized participants who receive at least one administration of study gas (NO or sham gas). Participants will be analyzed according to the treatment actually received, regardless of whether MDR bacterial infection is subsequently confirmed by antimicrobial susceptibility testing. Safety outcomes will be analyzed in the safety population.

The mITT-MDR population will include all participants who have at least one pathogen isolated from a baseline lower respiratory tract specimen that meets the prespecified MDR definition on antimicrobial susceptibility testing. Participants will be analyzed according to their randomized treatment assignment. The primary and secondary outcomes will be analyzed in the mITT-MDR population.

The PP-MDR population will include participants in the mITT-MDR population who complete at least 80% of the prespecified study-gas treatment sessions, have no major protocol deviations that could affect efficacy assessment, and complete assessment of the primary outcome. The PP-MDR analysis will be conducted only as a sensitivity analysis of the mITT-MDR analysis.

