#### Randomization and blinding

Participants will be randomly assigned in a 1:1 ratio to the high-dose inhaled NO group or the control group using a computer-generated simple randomization sequence. Allocation concealment will be maintained by an independent unblinded research staff member who is not involved in participant screening, clinical care, outcome assessment, data collection, or statistical analysis and who will retain the randomization codes.

Both groups will use identical NO delivery devices, respiratory circuit connections, treatment frequencies, and treatment durations. In the high-dose inhaled NO group, the device will operate in its standard mode to deliver the protocol-specified NO concentration. In the control group, the device will operate in a sham NO research mode. This mode will maintain the same user interface, operating procedures, and display of study-related parameters as in the intervention group, but will deliver gas containing no NO (NO concentration, 0 ppm).

For each treatment session, the independent unblinded research staff member will perform device connection, mode selection, parameter setting, and operational verification. This staff member will not participate in clinical care, outcome assessment, data collection, or statistical analysis and will not disclose device mode or treatment allocation to other study personnel or the clinical team. Participants, treating physicians, bedside clinical staff, outcome assessors, data collectors, and statisticians will remain blinded to treatment allocation.

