#### Sample size

As no previous studies have reported the effect of high-dose inhaled NO on CPIS outcomes in patients with severe pneumonia caused by MDR bacteria, the sample size was estimated using preliminary retrospective data from our center. These data included four patients who received high-dose inhaled NO and 11 patients who received standard treatment. The between-group difference in CPIS was 3 points, with a standard deviation of 4 points. Assuming a two-sided α of 0.05 and a β of 0.20 (80% power), at least 28 participants per group are required, for a total of 56 participants. Allowing a 10% dropout rate, the target sample size is 64 participants with confirmed MDR bacterial infection (32 per group). Assuming that 65% of patients with suspected MDR infection will have confirmed MDR bacterial infection, approximately 98 patients with suspected MDR infection will need to be enrolled.

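### Safety is assigned to one pooled set in which up to about 35% may have gas stopped by design, so harms that accrue with sessions may be understated for the planned 5-day course

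*Protocol article*

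**What the plan says.** Four parts of the protocol article bear on this.

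- **Interventions:** treatment is two sessions a day for 5 days, so 10 sessions. Once susceptibility results are available, confirmed participants continue. For the others, "the study intervention administered solely for research purposes will be discontinued in both groups". Permanent discontinuation of study-gas treatment repeats this rule and keeps those who stop in follow-up.
- **Sample size:** "Assuming that 65% of patients with suspected MDR infection will have confirmed MDR bacterial infection". On that basis the plan is to enrol about 98.
- **Analysis of populations:** the safety population is all randomized participants with at least one administration of NO or sham gas, analysed by treatment received, "regardless of whether MDR bacterial infection is subsequently confirmed by antimicrobial susceptibility testing. Safety outcomes will be analyzed in the safety population". Primary and secondary outcomes go to mITT-MDR. PP-MDR serves only as a sensitivity analysis of mITT-MDR.
- **Statistical analysis:** MetHb and NO2 exceedances, airway events and AKI are compared as counts and percentages of participants. No account of sessions received is mentioned.

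The Subgroup and sensitivity analyses section covers the primary outcome only. The abstract makes the same split between efficacy and safety populations.

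**The concern.** The stopping rule creates two exposure groups in each arm: participants meant to receive 10 sessions, and participants given only the sessions delivered before a negative susceptibility report. Safety pools them, while efficacy uses only the confirmed group. Benefit and harm are therefore estimated in sets whose gas exposure differs by design.

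The direction matters. The Discussion says the trial will examine whether NO improves outcomes without more adverse reactions. If a harm needs repeated sessions to appear, under-exposed participants lower the NO-arm percentage. Because both arms stop by the same rule, they also pull the NO-versus-sham difference towards zero. For a conclusion of no added harm, that error favours the treatment.

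**Working it through.** **The plan's own figures.** The inputs from the Sample size section are "The between-group difference in CPIS was 3 points, with a standard deviation of 4 points" and "Assuming a two-sided α of 0.05 and a β of 0.20 (80% power), at least 28 participants per group are required".

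- n per arm = 2 × (1.960 + 0.842)² × 4² / 3² = 27.9, so 28, or 56 in total.
- With 10% dropout, 28 / 0.90 = 31.1, so 32 per arm, or 64 in total.
- At 65% confirmation, 64 / 0.65 = 98.5. The plan states about 98.

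The chain reproduces. It implies 98 × 0.35 = 34.3, so about 34 of 98 participants unconfirmed. With 1:1 allocation that is about 17 per arm.

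**Inputs the protocol does not give.** These are the time to the susceptibility result and the way risk builds up over sessions. I assume that s = 2, 4, 6 or 8 sessions are delivered before stopping, and that per-session risk is constant and independent.

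**Mean exposure.** 0.65 × 10 + 0.35 × s = 7.2, 7.9, 8.6 or 9.3 sessions, against 10 planned.

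**Dilution.** Let R be the risk over 10 sessions.

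- Per-session risk: p = 1 − (1 − R)^(1/10)
- Short-course risk: R_s = 1 − (1 − p)^s
- Pooled incidence: 0.65 × R + 0.35 × R_s

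For R = 10% and s = 4: p = 1.05%, R_s = 4.13%, and pooled incidence = 6.50% + 1.45% = 7.9%.

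| Sessions before stop | R = 5% | R = 10% | R = 20% | R = 30% | Pooled / R |
|---|---|---|---|---|---|
| 2 | 3.6% | 7.2% | 14.5% | 21.9% | 0.721–0.730 |
| 4 | 4.0% | 7.9% | 16.0% | 24.2% | 0.792–0.805 |
| 6 | 4.3% | 8.6% | 17.4% | 26.2% | 0.862–0.875 |
| 8 | 4.7% | 9.3% | 18.7% | 28.2% | 0.931–0.940 |

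The relative shortfall runs from 1 − 0.940 = 6% to 1 − 0.721 = 28%. Starting instead from a 2% per-session risk, the full-course risk is 1 − 0.98^10 = 18.3%. The pooled figure is 14.6% (s = 4) to 15.9% (s = 6).

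**Difference between arms.** If the harm does not occur under sham, the difference equals the NO-arm incidence and the same ratios apply. If there is a background rate that does not depend on gas and simply adds to the gas-related risk, it cancels in the difference and the gas-related excess is scaled by these ratios. The NO-arm percentage itself then falls by less in relative terms.

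**Where the effect vanishes or shrinks.**

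- If the harm arises at the first session, R_s = R and the ratio is 1.
- If results arrive after day 5, s = 10 and the ratio is 1.
- The shortfall equals the share stopped early × (R − R_s). The 65% refers to suspected cases, and the Participants section also admits patients already confirmed. Their number is not given, so 35% is an upper figure and the shortfall falls in proportion.

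**The case against.** The strongest reply is that nothing quoted is an error. An all-treated safety set analysed by treatment received is standard, omits no exposed patient, and reflects a strategy that starts gas on suspicion. Extra safety tables are often left to an analysis plan, and one is mentioned under Data Availability but not shown. All this stands as a reason to keep the set primary and to rate the point low. It does not remove the point, because the article itself fixes the safety set and names no other.

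A reader might infer that efficacy is measured in full-course patients. The text does not support that. mITT-MDR has no completion requirement, and confirmed participants who stop for repeated exceedances, a suspected reaction, withdrawal or clinical judgement remain in it. The 80% session rule belongs to PP-MDR. A confirmed-MDR safety table would therefore be closer to the planned exposure, but not a pure 10-session result.

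The constant-risk model also does not fit every outcome. MetHb and NO2 thresholds may be crossed at the first session. If patients differ in their tendency to MetHb rise, events cluster early and dilution shrinks. AKI and creatinine carry background risk in critically ill patients.

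Precision is limited too. At 2% per session the gap is 18.3 − 15.9 = 2.4 to 18.3 − 14.6 = 3.7 points. The standard error in 32 NO participants is √(0.183 × 0.817 / 32) = 6.8 points. The added table would align the populations and show the exposure, but could not prove the dilution.

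**Conclusion.** The point holds as a possible understatement, not a certain one. On the plan's 65% figure, up to about 35% of suspected cases, about 34 of 98, would have gas stopped by design if results arrive before day 5. No safety result is specified for the group in which benefit will be claimed. For harms that build up with sessions, the pooled incidence and the arm difference may fall short of the 5-day-course risk by about 6% to 28% in relative terms. This assumes results after 2 to 8 sessions, constant independent per-session risk, and nobody confirmed at entry.

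A reader might go further and conclude that reported harm rates will be too low, or that the confirmed set should replace the all-treated set. Neither follows. The first depends on a time to result and a risk pattern that the protocol does not give. The second would drop harms in about 17 exposed NO participants: with zero events, the one-sided 95% upper limit loosens from 1 − 0.05^(1/49) = 5.9% to 1 − 0.05^(1/32) = 8.9%. This is a cheap improvement, not a correction of a wrong rule.

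**What to change.** Keep the all-treated safety population as the primary safety set. Under Analysis of populations, add two statements:

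1. Safety outcomes are also reported by arm in confirmed-MDR participants who received at least one study-gas administration.
2. MetHb and NO2 exceedances are also reported per session delivered.

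State benefit-risk from the all-treated and confirmed-MDR results side by side, not from the confirmed set alone.

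No new data are needed: Safety monitoring already provides for MetHb at each session, continuous NO2 and daily renal function. The cost is a few lines of text, one further set of tables, and wider intervals in those tables at about 32 per arm.

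### Deaths among gas-exposed participants whose MDR infection is not confirmed enter no specified final between-arm analysis

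*Protocol article*

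**What the plan says.** Under Secondary outcomes the protocol article lists "In-hospital mortality, ICU mortality, and 28-day mortality". Analysis of populations then fixes where these are analysed: "The primary and secondary outcomes will be analyzed in the mITT-MDR population". The Abstract says the same. The mITT-MDR population needs a baseline lower respiratory isolate that meets the MDR definition on susceptibility testing.

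The safety population is wider. It holds every randomised participant with at least one administration of NO or sham gas, whether or not MDR is later confirmed, but only the safety outcomes are assigned to it. Those are methaemoglobin thresholds, the NO₂ threshold, serum creatinine, airway hyperreactivity and, last on the list, "Incidence of acute kidney injury (AKI), including stages 1, 2, and 3, during hospitalization". Death is not among them.

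Safety monitoring says "Serious adverse events will be reported within 24 h" and gives the DSMB a set of triggers for ad hoc review. Permanent discontinuation of study-gas treatment names non-confirmation of MDR as one reason for stopping. It adds that participants who discontinue stay in follow-up and enter an intention-to-treat analysis.

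**The concern.** Study gas starts within 24 h of enrolment (Interventions). A participant enrolled on suspicion can therefore be exposed before susceptibility results arrive, and gas is stopped only once MDR is found not to be confirmed. The protocol accepts that these participants matter for harm, since it puts them in the safety population on purpose. It then leaves the most serious harm off that population's outcome list.

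For a high-dose inhaled gas in ventilated patients, all-cause death is the harm a reader will look for first. An analysis that follows the stated rules exactly could report methaemoglobin, NO₂, renal and airway findings in everyone exposed, and mortality only in the confirmed subset. Nothing in the stated plan would then show whether deaths among the remaining exposed participants were balanced between arms.

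**Working it through.** **1. Reproducing the planned numbers (Sample size).** The inputs are "The between-group difference in CPIS was 3 points, with a standard deviation of 4 points", two-sided α 0.05, 80% power and 1:1 allocation.

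- Per group, normal approximation: n = 2 × (1.96 + 0.84)² × 4² / 3² ≈ 27.9, so 28. This matches the stated 28 (a t-test calculation gives 29).
- 10% dropout: 28 / 0.90 = 31.1, so 32 per group and 64 in total. This matches.
- 65% confirmation: 64 / 0.65 = 98.5, stated as about 98. This matches within rounding.

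**2. Participants outside the mortality comparison.** 98 − 64 = 34, and 34 / 98 = 34.7% (equivalently 98 × 0.35 = 34.3). This is an upper planning figure for two reasons. The 65% applies to suspected cases, whereas Participants also admits patients already confirmed. It also assumes that everyone enrolled receives at least one session. If 98 are enrolled and a larger share of all participants is confirmed:

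| Share confirmed | Outside mITT-MDR |
|---|---|
| 65% | 98 × 0.35 = 34.3 |
| 80% | 98 × 0.20 = 19.6 |
| 90% | 98 × 0.10 = 9.8 |

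**3. Deaths outside the comparison.** The protocol gives no mortality rate, so 20% to 40% is an assumption. With 34 participants: 34 × 0.20 = 6.8 and 34 × 0.40 = 13.6, or about 7 to 14 deaths. With 19.6 participants: 3.9 to 7.8. With 9.8: 2.0 to 3.9.

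**4. Precision.** The 95% half-width for a risk difference is 1.96 × √(2p(1 − p)/n), with n per arm and a common rate p.

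| Assumed p | n = 32 (mITT-MDR) | n = 49 (all 98) |
|---|---|---|
| 20% | 19.6 points | 15.8 points |
| 40% | 24.0 points | 19.4 points |

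Both columns are imprecise. The gain that matters is coverage of everyone exposed; the narrower interval is secondary.

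**5. The sections side by side.**

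- Secondary outcomes with Analysis of populations: mortality is analysed in mITT-MDR.
- Safety outcomes with Analysis of populations: all exposed participants are covered, but death is not an outcome.
- Statistical analysis: mortality is listed for a chi-square or Fisher test, with no other population named for it.
- Permanent discontinuation: those who stop, including for unconfirmed MDR, are promised a place in an intention-to-treat analysis.
- Analysis of populations: three populations are defined (mITT-MDR, PP-MDR, safety). The first two require confirmed MDR, and the third is analysed by treatment received.

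The first three leave the deaths in question without a final analysis. The last two disagree on whether these participants are analysed by assigned arm at all.

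**The case against.** The strongest reply is that these deaths are not ignored. An independent DSMB reviews safety data every 6 months. Its triggers include an unexpected death at least possibly related to study gas and an imbalance between groups in serious adverse events, and neither is limited to confirmed MDR. The discontinuation section also says those who stop are kept in an intention-to-treat analysis. A reader might infer that these deaths enter no between-arm comparison of any kind. The documents do not support that. What stands is narrower: the DSMB rules govern trial conduct and are not a reported final comparison, and the intention-to-treat sentence refers to a population that the protocol never defines.

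A reader might also infer that serious adverse events will never be compared between arms. That cannot be claimed either. Their tabulation is commonly left to the statistical analysis plan, which is not shown, and the events are collected. The mortality point differs because the article itself assigns mortality to a population.

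Two further objections are fair. Restricting efficacy outcomes to confirmed MDR is a deliberate and defensible choice, and nothing here argues against it. Unconfirmed participants stop gas early, so pooling them may dilute a dose-related harm. That is a reason to show results by confirmation status as well; it does not justify leaving the deaths out.

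**Conclusion.** The point holds for mortality. As written, deaths among exposed participants without confirmed MDR have no place in any specified final between-arm analysis, and the promised intention-to-treat analysis conflicts with the defined populations. On the planning figures this affects up to about 34 of 98 participants. A third is thus a ceiling that rests on the 65% confirmation rate and on all 98 being exposed; at 80% or 90% confirmed overall it falls to about 20 or 10. The 7 to 14 deaths depend wholly on the assumed 20% to 40% mortality. The gap in the text does not depend on any of these figures.

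**What to change.** - Keep mortality in mITT-MDR as the efficacy outcome.
- Under Safety outcomes, add 28-day all-cause mortality and, alongside it, the number and percentage of participants with at least one serious adverse event. Analyse both in the safety population by arm, according to treatment received as already stated there, with risk difference and 95% confidence interval.
- Report 28-day mortality by assigned arm in all randomised participants.
- Show these results by MDR confirmation status too, because exposure in the unconfirmed group may be partial.
- Reconcile the intention-to-treat sentence under Permanent discontinuation with Analysis of populations, either by defining that population or by naming the one that is meant.

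The cost is a few lines of text and a few more tables. Follow-up after discontinuation, 28-day mortality (Table 1) and serious adverse event reporting are already in the protocol, so no new data are needed.
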